# Comparative effectiveness of implementation strategies for Accelerating Cervical Cancer Elimination through the integration of Screen-and-treat Services (ACCESS study): protocol for a cluster randomized hybrid type III trial in Nigeria

**DOI:** 10.1186/s13012-024-01349-9

**Published:** 2024-03-11

**Keywords:** Africa, Nigeria, Cervical cancer, Implementation science, Women living with HIV, EPIS framework, Exploration, Preparation, Implementation, and Sustainment framework, RE-AIM

## Abstract

**Background:**

Despite the increased risk of cervical cancer (CC) among women living with HIV (WLHIV), CC screening and treatment (CCST) rates remain low in Africa. The integration of CCST services into established HIV programs in Africa can improve CC prevention and control. However, the paucity of evidence on effective implementation strategies (IS) has limited the success of integration in many countries. In this study, we seek to identify effective IS to enhance the integration of CCST services into existing HIV programs in Nigeria.

**Methods:**

Our proposed study has formative and experimental activities across the four phases of the Exploration, Preparation, Implementation, and Sustainment (EPIS) framework. Through an implementation mapping conducted with stakeholders in the exploration phase, we identified a core package of IS (Core) and an enhanced package of IS (Core+) mostly selected from the Expert Recommendations for Implementing Change. In the preparation phase, we refined and tailored the Core and Core+ IS with the implementation resource teams for local appropriateness. In the implementation phase, we will conduct a cluster-randomized hybrid type III trial to assess the comparative effectiveness of Core versus Core+. HIV comprehensive treatment sites (*k* = 12) will be matched by region and randomized to Core or Core+ in the ratio of 1:1 stratified by region. In the sustainment phase, we will assess the sustainment of CCST at each site. The study outcomes will be assessed using RE-AIM: reach (screening rate), adoption (uptake of IS by study sites), IS fidelity (degree to which the IS occurred according to protocol), clinical intervention fidelity (delivery of CC screening, onsite treatment, and referral according to protocol), clinical effectiveness (posttreatment screen negative), and sustainment (continued integrated CCST service delivery). Additionally, we will descriptively explore potential mechanisms, including organizational readiness, implementation climate, CCST self-efficacy, and implementation intentions.

**Discussion:**

The assessment of IS to increase CCST rates is consistent with the global plan of eliminating CC as a public health threat by 2030. Our study will identify a set of evidence-based IS for low-income settings to integrate evidence-based CCST interventions into routine HIV care in order to improve the health and life expectancy of WLHIV.

**Trial registration:**

Prospectively registered on November 7, 2023, at ClinicalTrials.gov no. NCT06128304. https://classic.clinicaltrials.gov/ct2/show/study/NCT06128304

**Supplementary Information:**

The online version contains supplementary material available at 10.1186/s13012-024-01349-9.

Contributions to literature
This study will be the first to test the effectiveness of tailored implementation strategies (IS) for cervical cancer screening and treatment (CCST) among women living with HIV in Nigeria.The study integrates two implementation science frameworks: The Exploration, Preparation, Implementation, and Sustainment (EPIS) Framework and Reach, Effectiveness, Adoption, Implementation, and Maintenance (RE-AIM) to guide implementation process, engage collaborators, and assess implementation outcomes.The ACCESS project advances a community-engaged collaborative approach to implementation strategy development and tailoring across diverse regions of an entire country for improving cancer control in low-and middle-income countries.The use of the implementation resource team approach engages collaborators through the EPIS process phases to refine and tailor implementation strategies for local appropriateness and facilitate the documentation of planned and ad hoc adaptations during the study.

## Background

Cervical cancer (CC) is the second most common cancer in women in Africa [1] and is a large contributor to cancer deaths in the region [2]. While age-standardized mortality trends have declined in high-income countries, mortality is rising in many low-income countries [3]. By 2030, CC will account for more than 106,000 deaths annually in Africa, an increase of 38% from the estimated 77,000 deaths in 2020 [4]. Compared with HIV-negative women, women living with HIV (WLHIV) are six times more likely to develop CC [5], and are at increased risk of mortality from CC [6–9]. About 25% of CC cases in Africa are diagnosed in WLHIV, and 21% are attributable to HIV [10]. With a 5-year prevalence of 22,500 cases [11] and 960,000 WLHIV [12], Nigeria has one of the largest burdens of CC and HIV in Africa.

CC is completely preventable. It is also curable if diagnosed and treated early. The availability of effective interventions, including human papillomavirus (HPV) vaccination and screening and treatment of precancerous lesions of CC [13], underpins the current global effort to eliminate CC as a public health problem [14]. The World Health Organization (WHO) has set measurable global targets of 90–70–90 (90% of girls fully vaccinated with HPV vaccine by 15 years of age, 70% of women screened using a high-performance test, and 90% of women identified with preinvasive cancer and invasive CC treated) to prevent and treat CC by 2030 [15].

CC screening and treatment (CCST) is an important evidence-based intervention for CC prevention and control. However, many African countries have not been able to implement and sustain organized national CC screening programs [16]. Although the availability of low-cost screening methods such as visual inspection with acetic acid (VIA) or Lugol’s iodine (VILI) for CC screening [17, 18] offers opportunities to improve early detection of CC in Africa, screening rates among women, including WLHIV, remain low [19]. In Nigeria, despite the recommendations of routine CC screening of WLHIV [20], studies have found screening coverage of < 10% among WLHIV [21–24]. CC screening in Nigeria is affected by several factors such as the unavailability of screening services, screening not being offered by healthcare providers, and poor awareness of the disease and screening services [25–28]. Efforts to improve the control of CC and other cancers in Nigeria have included the designation of one federal tertiary hospital in each of the country’s six geopolitical regions as oncology centers of excellence, where comprehensive cancer screening, diagnosis, and treatment can be accessed.

In low- and middle-income countries (LMIC) with a high burden of HIV, the integration of CCST services into the established HIV programs can improve CC prevention and control [29–31]. Investment in the HIV response has improved access to antiretroviral therapy (ART) in many African countries [32, 33]. For example, the US President’s Emergency Plan for AIDS Relief (PEPFAR) HIV care program in Nigeria has invested more than US $6 billion in Nigeria’s national HIV response [34]. PEPFAR has contributed to health systems strengthening through human capacity development, establishing electronic health management information systems, and providing state-of-the-art laboratories to adequately respond to the HIV epidemic and other diseases in Nigeria [35]. These existing infrastructures for HIV can be leveraged to deliver CCST services. Depending on the availability of physical and human resources, the integration of CCST services into HIV services may be within the same clinic or through referral [36].

While evidence suggests that the integration of CCST into HIV services is feasible and acceptable [36–40], it has not been widely implemented at scale or yielded the desired outcomes in many low-resource, high-burden countries, including Nigeria [15]. The gap in knowledge of effective implementation strategies (IS) to enhance integration of CCST into HIV services has limited its success and scale-up [30, 41]. Findings from previous reports [40, 42, 43] indicate that effective integration of CCST for WLHIV will require tailored IS that will simultaneously address multilevel barriers in the outer context of the country health systems and the inner organizational contexts of HIV clinics [44, 45].

Accordingly, guided by the Exploration, Preparation, Implementation, and Sustainment (EPIS) framework [44, 46], we will determine the barriers to and facilitators of CCST implementation and sustainment and identify and test promising implementation strategies to enhance the integration of CCST into existing HIV programs in Nigeria. EPIS is both a process and determinant framework that describes four phases of the implementation process to guide researchers and implementers in the process. We utilized the EPIS process phases to stage the study while also invoking consideration of determinants and mechanisms (i.e., barriers and facilitators). Determinants are identified in the outer system context (e.g., cultural and populations variation in regions), inner organizational context (i.e., clinic operations), innovation factors (i.e., characteristics of CCST), and bridging factors that connect outer and inner contexts [47]. Importantly, EPIS also recognizes the importance of relationships, interconnections, and linkages among and between actors in outer and inner contexts. Our implementation and clinical outcomes are informed by the Reach, Effectiveness, Adoption, Implementation, and Maintenance (RE-AIM) framework. As part of study development, the EPIS exploration phase was completed in which we collaborated with stakeholders in Nigeria who participated in the following: (1) identifying and ranking implementation barriers and facilitators and (2) matching and ranking IS to the identified determinants [48]. As shown in Table 1, the results from the implementation mapping and the refinement are a set of a core package of IS (Core) and an enhanced package of IS (Core+).

**Table 1 Tab1:**
[figure not shown]
Barriers and strategies from stakeholder implementation mapping and refinement

Our specific aims are as follows:Aim 1: Refine strategies to integrate CCST of cervical precancer within existing comprehensive HIV treatment programs.Aim 2: Determine the comparative effectiveness of the Core vs Core+ implementation strategies on CCST*.*Aim 3: Assess the sustainment of the integration of CCST into comprehensive HIV treatment programs.

## Methods

### Overview of study preparation and design

This is a cluster randomized trial using hybrid type III implementation-effectiveness study type [49] to assess the comparative effectiveness of a set of Core and enhanced (i.e., Core+) implementation strategies on the implementation and sustainment of cervical cancer screening and treatment for WHLIV. The hybrid type III design focuses primarily on testing IS effectiveness while observing clinical effectiveness outcomes [49]. HIV comprehensive treatment centers (*k* = 12) will be matched by region and randomized 1:1 to Core or Core+ strategies. We will assess both implementation and clinical outcomes and explore potential mechanisms that affect the study outcomes, including organizational readiness, implementation climate, CCST self-efficacy, and implementation intentions. The study is guided by two implementation science frameworks — EPIS and RE-AIM.

### Exploration, preparation, implementation, and sustainment (EPIS) framework

EPIS was selected because it is useful in guiding implementation in different settings including low-income countries [44, 46, 50]. Figure 1 shows the activities within each phase.

**Fig. 1 Fig1:**
[figure not shown]
EPIS framework activities and outer/inner contexts

Prior to grant submission and funding, we completed the *exploration phase* [48] where we used survey and modified nominal group techniques (NGT) [51] to conduct a rapid and facilitated implementation mapping [52] exercise. Collaborators identified and ranked barriers and identified, selected, and ranked implementation strategies starting with the Expert Recommendations for Implementing Change (ERIC) [53] and other identified additional strategies. The final set of strategies were selected to address the barriers to integration of CCST into HIV treatment programs to form the Core IS. Stakeholders identified two additional strategies to be included in the Core+ IS condition [48].

In the *preparation phase*, we refined the IS and convened implementation resource team (IRT) [54] meetings to further reflect on the refined Core and Core+ IS fit with local context. Implementation resource teams were first conceptualized and tested in the dynamic adaptation process model and the Interagency Collaborative Team model for scaling up evidence-based practices [54, 55]. The IRT for this study is a community-engaged co-creation collaborative comprising the research team and the doctors and nurses from the study sites. Twelve site research coordinators (SRCs) were also recruited and trained during this phase.

The process of refinement of our proposed implementation strategies occurred in two phases. In the first phase, the research team developed an IS table which included the identified implementation determinants (barriers/facilitators), the initially proposed IS for each determinant, a definition of each IS, the population targeted by the IS, the proposed actions for the IS, and the responsible person(s) for these proposed actions. For each IS, we discussed its feasibility and importance in addressing the implementation determinant based on the IRT’s current knowledge of the context in the implementation sites. For each IS that IRT identified as not being the most feasible or important to address the implementation determinant, we selected another IS from the same category in the ERIC grouping of implementation strategies [53], and we included some strategies not included in ERIC. The refined strategies are shown in Table 1.

In the second phase, 12 doctors and 12 nurses, 1 from each study site, participated in 2 focus-group discussions (FGDs) to further refine the IS. Each FGD was facilitated by a member of the research team with experience in qualitative data collection, using a semi-structured FGD guide, while two members of the research team took notes. Written informed consent was obtained from all the participants after reading the information about the study and the FGDs and given the opportunity to ask questions. Verbal consent was also obtained from the participants for the audio recording of the FGDs. The participants were presented with the refined implementation strategies table developed in the first phase and were asked to contribute to further refinement of the table, particularly tailoring the target population, planned actions, actor, dose, and mode of delivery. They were also asked to state if any of the IS or their activities would not be feasible at their sites. For any IS where the participants had different views about tailoring, discussions were held, and a consensus was reached. Each FGD lasted for about 2 h. Details of the further refined strategies are shown in Table 2. All of this work was in preparation for the cluster randomized trial to be described in the next section.

**Table 2 Tab2:** Implementation strategies

Arm	Strategy	Definition	Actor	Action	Target	Dose	Delivery
Core and Core+	Provide ongoing consultation	Provide ongoing support to address specific site CCST training needs	Practice-based Research Network Site clinical team	Conduct real-time support and periodic training sessions on CCST through the review of cases captured on AVIVA app (a mobile app that allows images (native cervix, acetic acid- and Lugol iodine-stained cervix) to be uploaded for expert’s review) [59]	Site clinical team	Clinic days (real time) Quarterly (periodic sessions)	Virtual
Core and Core+	Conduct educational meetings	Hold meetings among healthcare providers to improve CCST service provision	Site clinical team	Conduct site clinical review meetings on CCST cases, number screened and treated within review period and any other quality improvement issue	Site clinical team	Monthly	In-person
Core and Core+	Strengthen ties with stakeholders	Hold meetings with policymakers and donor partners to facilitate availability of commodities and equipment for CCST	Research team	Conduct stakeholder meetings	Ministry of Health PEPFAR IPs Site clinical teams Site medical directors	Quarterly	Virtual
Core and Core+	Strengthen referral system	Facilitate referral and easy navigation at referral centers to ensure referred WLHIV with suspected cancer complete referral	Site clinical team	Identify and prepare individuals as referral coordinators to track and support easy navigation at referral centers	WLHIV	Continuous	In-person
Core and Core+	Prepare patients to be active participants	Prepare patients to be active participants in their care	Site clinical team	Distribute flyers/leaflets/flip charts on CCST	WLHIV Partners of WLHIV	Continuous	In-person
Core+	Community engagement through Healthy Beginning Initiative (HBI)	Engage communities of WLHIV through a congregational-based approach [60–62] to educate and create awareness about CC and CCST	Site clinical team Community health team	Conduct HBI incorporating CC and CCST education at HIV support group meetings	PLHIV	Quarterly	In-person
Core+	Engage patient using an mHealth platform	Use patient-held smartcard [63, 64] linked to an mHealth platform to record CCST services and track and send appointment reminders to WLHIV	Research team/clinical team	Scan patients’ smartcards and capture CCST information at every study visit Send appointment reminders to patients	WLHIV	Continuous	In person

*CC* cervical cancer, *CCST* cervical cancer screening and testing, *IP* implementing partners, *PLHIV* people living with HIV, *WLHIV* women living with HIV

In the *implementation phase*, we will implement the Core and Core+ IS and test their comparative effectiveness on select implementation outcomes while collecting data on potential mechanisms of effects and clinical effectiveness outcomes. We will also catalog any ad hoc adaptations and contextual factors affecting implementation, services, and clinical outcomes with a focus on sustainment.

In the *sustainment phase*, we will assess sustainment of CCST and IS at each site and provide summaries to stakeholders regarding the planned and ad hoc adaptations that occurred during implementation.

### Reach, Effectiveness, Adoption, Implementation, and Maintenance (RE-AIM)

We selected RE-AIM as our evaluation framework for assessing individual- and setting-level outcomes important to program impact and sustainment [56, 57]. As shown in Table 3, we address relevant RE-AIM constructs: Reach, Effectiveness, Adoption, Implementation, and Maintenance (also known as Sustainment) [56, 57]. In operationalizing these five dimensions, we adapted the metrics recommended by the Integrative Systems Praxis for Implementation Research (INSPIRE) model [58]. We defined the constructs as follows: reach (screening rate); clinical effectiveness (posttreatment screen negative); adoption (uptake of IS by study sites); IS fidelity (degree to which the IS occurred according to protocol); implementation clinical intervention fidelity (delivery of CC screening, onsite treatment, and referral according to protocol); and maintenance (or sustainment) (the degree to which integration of CCST continued).

**Table 3 Tab3:** Measures by EPIS phase and study aims

Aim	Construct	Measurement	Data source
EPIS preparation and implementation phases			
2	Reach (EPIS inner context)	•% WLHIV who had CC screening	Health records Participant survey
2	Effectiveness (EPIS inner context)	•% WLHIV treated for preinvasive cancer who had negative posttreatment follow-up screening	Health records Participant survey
2	Adoption	•% study sites that used AVIVA app to capture CC cases for real-time support •% study sites that participated in the periodic review training sessions on CCST •% study sites that initiated monthly educational meetings •% study sites that participated in the quarterly stakeholder meetings •% study sites that identified a referral coordinator to follow through with referred WLHIV with suspected cancer and ineligible lesions for treatment •% study sites that distributed flyers/leaflets/flipcharts on CCST in clinics •% study sites (Core+) that conducted HBI at support group meetings •% study sites (Core+) that captured CCST data of recruited WLHIV on smart card •% study sites (Core+) that send appointment reminders to patients using the mHealth platform	Survey Documented records
2	Implementation strategy fidelity	•(QUANT) 7 items (for Core) and 11 items (for Core+) with subscales, degree that components of each strategy were implemented in terms of adherence, exposure, quality, and engagement	Survey Documented records Periodic reflection
2	CCST intervention fidelity (EPIS inner context)	•% WLHIV with preinvasive cancer eligible for treatment who had same-day treatment •% WLHIV treated for preinvasive cancer who had posttreatment follow-up screening at 12 months •% WLHIV with suspected cancer or lesions ineligible for treatment referred	Health records Participant survey
2	Organizational readiness for CCST	•(QUANT) organizational readiness for implementation (ORIC)	Provider survey
2	Implementation climate (EPIS inner context)	•(QUANT) six items with three subscales, degree that CCST is expected, supported, and rewarded	Provider survey

#### Site selection

The study will leverage the 21 comprehensive HIV treatment sites across the six geopolitical zones of Nigeria that have been designated as Nigeria Implementation Science Alliance (NISA) Model Innovation and Research Centers (NISA-MIRC) [65]. The NISA-MIRC sites are part of the ICON-3 Practice-based Research Network which is made up of the 21 NISA-MIRCs and the 6 Regional Centers of Excellence. The NISA-MIRCs have over 60,000 WLHIV in care who are eligible for enrollment into clinical trials and other implementation research studies [65]. Our proposed study will be anchored at 12 sites (see Figure 2 and Additional file 1) from the 21 NISA-MIRCs. The criteria for selection were based on the following: (1) geographical spread (two sites per region), (2) highest proportion of consented WLHIV for enrolment into clinical trials and other implementation research studies, and (3) match of the same type of site per region (secondary or tertiary).

**Fig. 2 Fig2:**
[figure not shown]
12 NISA-MIRCs selected for ACCESS study

#### Randomization

The unit of randomization will be the sites. Each site represents a cluster in the randomization representing the clinic site and the WLHIV receiving treatment at the site. We will conduct simple random allocation with the sites randomized to either the Core or Core+ IS. There are six geographic regions in Nigeria, and sites will first be matched by region, and then each site in a matched pair will be randomized to Core or Core+ IS. A random number generator will be used to assign the sites. A flow diagram for the randomization and intervention allocation is shown in Figure 3. The healthcare workers and the patients will be blinded to whether their sites are allocated to the core package of IS or an enhanced package of IS.

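### The stated blinding of staff and patients contradicts how Core+ was designed and is delivered; the primary outcome, which lists self-report as a source, is open to reporting bias of unknown direction

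*Protocol article*

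**What the plan says.** Randomization states the blinding without qualification: "The healthcare workers and the patients will be blinded to whether their sites are allocated to the core package of IS" or the enhanced package.

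The account of the preparation phase, in the section on the EPIS framework, describes what site staff did before the trial. The implementation resource team is a group "comprising the research team and the doctors and nurses from the study sites", and it held "meetings to further reflect on the refined Core and Core+ IS fit with local context". In the next round, "12 doctors and 12 nurses, 1 from each study site, participated in 2 focus-group discussions (FGDs) to further refine the IS", and "The participants were presented with the refined implementation strategies table developed in the first phase". They were asked to tailor that table and to say what would not work at their own site.

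Table 2 gives two strategies to Core+ only:
- Healthy Beginning Initiative (HBI) education at HIV support group meetings, with the site clinical team and a community health team as actors.
- A patient-held smartcard linked to an mHealth platform. The research and clinical teams scan the card and "capture CCST information at every study visit", and reminders go to the women.

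Reach is the primary outcome (Sample size and power calculation; Data analysis). Table 3 measures it as the percentage of "WLHIV who had CC screening" and names two sources, health records and participant survey. Under Aim 2, Data collection says that follow-up questionnaires supplement the electronic medical records. Under Schedule of measurement, receipt of screening is assessed 12 months after enrollment.

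**The concern.** A trial described as blinded at provider and participant level invites readers to discount reporting bias. If that blinding cannot exist, the protection is only apparent. Here the primary outcome can draw on what women say about their own screening, and the article describes no masked assessment of it. Women in one arm get extra education about screening, a card and reminders, all of which could change how they answer a survey question on screening. The provider scales (organizational readiness, implementation climate, implementation intentions and self-efficacy) are also self-report, by staff who can tell which package they are working with.

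**Working it through.** **Step 1: is the blinding sentence compatible with the rest of the article?**

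| Group | What the sentence requires | What the article describes |
|---|---|---|
| Healthcare workers | Not knowing whether the site has Core or Core+ | Site doctors and nurses discussed both packages; one doctor and one nurse from all 12 sites helped tailor the strategies; Core+ clinical teams are actors for HBI and smartcard scanning |
| Patients | Not knowing whether the site has Core or Core+ | Core+ women hold a smartcard, get reminders and are a target of HBI sessions; Core women have none of these |

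For staff the two accounts cannot both be true. Clinicians who helped shape both packages will recognise the one that they deliver, and at Core sites they will notice which components are absent. A Core-site worker who took no part in the preparation might be unaware, but the sentence covers healthcare workers without exception.

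For patients the contradiction is narrower. A woman may not know that a second package exists or that hers is the larger one. She does know about the card, the reminders and the sessions, and that exposure is what could affect her answers.

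**Step 2: how large could the effect on reach be?**

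The article gives no over-reporting rate, so everything below is an assumed scenario. Inputs from Sample size and power calculation: Core rate 14%, Core+ rate 34%, target difference 20 points. The power figures there are not in dispute. With 200 women per site, 6 sites per arm and a t test on 10 degrees of freedom, ICC 0.06 gives a design effect of 1 + 199 × 0.06 = 12.94, an effective 1200 / 12.94 = 92.7 women per arm and 83.97% power (stated 84%). ICC 0.07 gives 78.56% (stated 78.6%).

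Let p be true reach and f the share of unscreened women who report a screening. If a self-report alone counts:

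observed reach = p + (1 − p) × f

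With the same true p in both arms, the spurious difference is (1 − p) × (f in Core+ − f in Core). At p = 0.14:

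| f in Core | f in Core+ | Observed Core | Observed Core+ | Spurious difference |
|---|---|---|---|---|
| 0% | 5% | 14.0% | 18.3% | 4.3 points |
| 5% | 10% | 18.3% | 22.6% | 4.3 points |
| 0% | 10% | 14.0% | 22.6% | 8.6 points |
| 5% | 15% | 18.3% | 26.9% | 8.6 points |
| 10% | 20% | 22.6% | 31.2% | 8.6 points |

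Only the excess matters here: 0.86 × 0.05 = 0.043 and 0.86 × 0.10 = 0.086. Against the 20-point target these are 21.5% and 43%. An excess of the same size in Core would give the same figures with the opposite sign.

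At the planned rates of 14% and 34%:
- f of 5% and 10%: 18.3% against 40.6%, a difference of 22.3 points.
- f of 5% and 15%: 18.3% against 43.9%, a difference of 25.6 points.
- f of 10% in both arms: 22.6% against 40.6%, a difference of 18.0 points.

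So over-reporting can inflate the effect, or shrink it when it is equal in both arms.

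**The case against.** The best defence concedes the staff wording and resists the rest. Packages that people can see can rarely be blinded, no calculation in the article uses the blinding, and an article may leave the ranking of data sources to the full protocol. That last point stands: the absence of a ranking is not itself an error, and the article nowhere says that a self-report alone counts as a screening. The blinding sentence is different, because it is stated and it is wrong.

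A reader might infer more than the documents support:
- *That patients must know their arm.* The consent text is not shown, so they may not know the label.
- *That the focus-group table separated the arms.* The described contents name no arm column. The evidence that staff knew of both packages is the resource team's discussion of Core and Core+.
- *That screenings are recorded more often in Core+ through the smartcard.* Table 3 does not list the smartcard as a source for reach, and whether its entries feed the health records is not stated. Both arms also share the AVIVA image app and monthly reviews of numbers screened.
- *That the bias must favour Core+.* Core women are also enrolled, surveyed and given educational materials, and equal over-reporting would work against Core+.

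**Conclusion.** The blinding sentence is contradicted by the article's own procedures: fully for healthcare workers, and for patients as regards what they receive, though not necessarily the name of their arm. The contradiction matters because reach lists self-report among its sources and no masked assessment is described. The resulting bias is possible but not shown. The range of 4.3 to 8.6 points is hypothetical and rests on three assumptions: true reach of 14% in both arms, self-report alone counting as a screening, and a 5- to 10-point excess of false reports among unscreened Core+ women. None of the stated sample size or power figures changes.

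**What to change.** - Replace the blinding sentence with a statement that sites, providers and participants are not blinded, and that outcome abstraction and analysis are done without arm labels where feasible.
- Define primary reach, in both arms, as a screening documented in clinic health records within 12 months of enrollment, abstracted in the same way and never from the Core+-only smartcard platform alone.
- Use participant-reported screening, including screening done elsewhere, as a sensitivity analysis.
- Report the provider scales as unblinded self-report.

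The cost is a change of wording and an outcome definition. Records and questionnaires are already collected, so no extra sites, visits or participants are needed. The downside is that screenings done elsewhere drop out of the primary analysis. The loss need not be equal by arm, since HBI education in support groups could change where Core+ women are screened. The sensitivity analysis should therefore show, by arm, how many screenings are known only from self-report.
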